#### Control group (SEMS)

Stents used in this study must be self-expanding, partially covered metal stents (CE certified - CE0197). The product will be narrowed down to a few models, but the final decision regarding the stent type and size will be left up to the endoscopist. The stent may be secured in its position by using clips or endoscopic suturing techniques. To achieve optimal coverage and seal of the leak, the flare ends of the stent need to be proximal and distal to the leak. In case of stent dislocation or migration, the stent may be repositioned and fixed or replaced by another model or size with better adjustment. This scenario will be documented as a complication. After successful stent placement, a triple lumen nasojejunal feeding tube suitable for intestinal feeding and gastric decompression is inserted. The stent will be removed or replaced after 21 days (±2 days).

#### Image-guided drainage insertion

Regardless of the group allocation, each patient receives a CT scan of the thorax and abdomen, which should preferably be performed prior to study treatment. Oral and intravenous CT contrast is used to diagnose possible fluid collections. In case of insufficiently drained fluid collections, an ultrasound- or CT-guided drainage will be inserted by a radiologist.

#### Supportive therapy

All patients receive supportive therapy such as transfusions of red cell concentrates or analgesia according to international intensive care standards and guidelines. Regardless of the group allocation, an enteral nutrition regimen is implemented via the jejunal lumen whereas continuous drainage of reflux with a suction of 10mmHg is ensured via the gastric lumen. Immediately after diagnosis of an anastomotic leak, all patients receive a calculated broad-spectrum anti-infective therapy and close monitoring, if necessary by intensive care. All intensive care treatments, including organ replacement therapies, may be applied as required.

### Follow-up

Following the primary endoscopic intervention, the patient will be treated according to the clinic’s standard operating procedures. If the patient’s clinical status does not improve within 72 h, endoscopic reevaluation and/or another CT scan will be performed. In case of new fluid collections, a drainage will be inserted. If endoscopy shows necrosis or severe ischemia of the interponate or a significant increase of the anastomotic leak size, a surgical revision will be evaluated by the treating physician taking into account the patient’s clinical status.

During the hospital stay, the following data are determined on days 3, 7, 14, 21, and 28 and then weekly (±1 day) after the diagnosis of anastomotic leakage as illustrated in Table 1: vital signs, SOFA score, duration of ventilation, leukocytes, CRP, and procalcitonin value, if applicable [22]. All relevant endoscopic, surgical, and non-surgical complications throughout the hospital stay including postoperative death will be documented in the CRF (Table 1). Follow-up examinations are performed 3 and 6 months (±14 days) after inclusion (Table 1). In addition to assessing the quality of life and the clinical status, the following details are documented on follow-up visits: body weight, Karnofsky index, presence of dysphagia or a symptomatic stenosis, oncologic status (relapse/remission), and tumor-specific therapy, if applicable. The recurrence rate and mortality including the cause of death will be documented beyond the last study visit contacting the treating physician or the patient.

**Table 1 Tab1:** Trial events according to treatment and follow-up plan

		Intervention phase		Follow-up (time after informed consent)		
Trial checkpoint	Screening	Prior to treatment	Hospital stay after inclusion	3 months (± 14 days)	6 months (± 14 days)	12 months (± 14 days)
**Informed consent**	X					
**Inclusion/exclusion criteria**	X					
**Medical history, physical examination, vital signs**	X^a^	X	X^b^	X	X	X
**Diagnostic upper GI endoscopy**		X				
**CT scan**		X	(X)		x	
**ECG**	X					
**Laboratory tests**	X	X	X^b^	X	X	X
**Operative report**		X	X			
**Postoperative complications, treatment failure**		X	X			
**SOFA score**		X	X^b^			
**QoL questionnaire**	X		X^c^	X	X	X
**Treatment costs**			X			
**Monitoring of SAE**		X (from randomization to discharge from hospital + 30 days)				
**Overall survival**		X				

^a^At inclusion with detailed medical history and extensive physical exam, otherwise only vital signs, weight, and Karnofsky index

^b^On days 3, 7, 14, and 21 (±1 day)

^c^On day 10 and prior to discharge from hospital

To reduce the rate of loss of follow-up, we chose short-term aspects as primary outcome parameters and planned the follow-up visits according to the routinely conducted quarterly oncologic follow-up exams in each center.

### Data collection

#### Patient characteristics

All preoperative screening parameters, such as patient’s history (smoking status, alcohol intake, presence of diabetes, and previous thoraco-abdominal operations), clinical status (body height, body weight, blood pressure, heart rate, activity index, Karnofsky index, and ASA score), and tumor-specific parameters (histological confirmation of esophageal cancer, preoperative TNM and RECIST classification, results of clinical staging exams and tests conducted according to the national guideline for esophageal cancer (German S3 Guideline, 2018) and previous tumor-specific treatment), as well as all inclusion and exclusion criteria, will post hoc be included in the CRF.

#### Feasibility of a RCT

To determine the feasibility of a RCT, screening and recruitment logs are used to evaluate the recruitment and retention rate. Moreover, the number of patients not fulfilling the inclusion and exclusion criteria is documented to evaluate the suitability of the parameters.

### Effect evaluation

#### Primary effect measure

The primary endpoint of this study is the subjective quality of life assessed by the patient using a systematic and validated questionnaire from the European Organisation for the Research and Treatment of Cancer (EORTC QLQ C30, EORTC QLQ-OES18 questionnaire), which incorporates nine multi-item scales: five functional scales (physical, role, cognitive, emotional, and social), three symptom scales (fatigue, pain, and nausea and vomiting), and a global health and quality-of-life scale [23–25]. The evaluation will be performed at screening, after randomization before treatment, day 7 (±2) after randomization, upon discharge from the hospital, and 1 (±5 days), 3, and 6 months after randomization (±14 days). After inclusion, data will be transferred to the CRF.

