### Patients

This study will be conducted at the University Hospital of Cologne and the University Medical Center Hamburg-Eppendorf and include a total of 40 patients (n=40). The number of patients is estimated in order to show the feasibility of the trial protocol and to provide data to calculate the sample size for a larger randomized prospective interventional trial.

All patients with resectable esophageal cancer will be screened for eligibility to be enrolled in the study. Informed consent will be obtained preoperatively before the inclusion criterion of an anastomotic leak is satisfied.

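### The primary quality-of-life endpoint has two conflicting questionnaire schedules: three of the seven assessments in the endpoint definition are not scheduled in Table 1, and the follow-up clock starts at a different event

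*Protocol article*

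**What the plan says.** The protocol article gives the timing of the primary endpoint in two places.

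- **Effect evaluation, Primary effect measure.** The early assessments are: "The evaluation will be performed at screening, after randomization before treatment, day 7 (±2) after randomization, upon discharge from the hospital". The later ones are "1 (±5 days), 3, and 6 months after randomization (±14 days". That makes seven, and the fixed post-randomisation times are counted from randomisation.
- **Follow-up, Table 1, row "QoL questionnaire".** There is a mark at screening, none in the column before treatment, a footnoted mark for the hospital stay, and marks at 3, 6 and 12 months. Footnote c reads "On day 10 and prior to discharge from hospital". That makes six. The column header for the later visits is "Follow-up (time after informed consent".

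The running text of the Follow-up section names a further origin: "Follow-up examinations are performed 3 and 6 months (±14 days) after inclusion". It adds that quality of life is assessed at those visits.

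On consent, the Patients section states: "Informed consent will be obtained preoperatively before the inclusion criterion of an anastomotic leak is satisfied". The exclusion criteria remove leaks within 48 hours of surgery and leaks more than 4 weeks after it. No sentence says whether the definition or the table takes precedence.

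**The concern.** A primary endpoint needs one set of measurement times and one clock. Here the endpoint definition and the schedule of events disagree on both. Three consequences follow.

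1. **The baseline.** Screening quality of life is recorded before surgery. The form between randomisation and treatment is the only one that describes the patient with a leak but before stent or vacuum therapy. Table 1 does not schedule it, and it cannot be collected later.
2. **The early fixed times.** The notes to Table 1 explain that short-term aspects were chosen as primary to limit loss to follow-up. Yet the two sources differ on every fixed-day assessment in the first month. The early post-treatment assessment they share is discharge. That is not a fixed time, and length of stay is itself a secondary endpoint that may differ by arm.
3. **The later visits.** Counted from a preoperative consent, a 3-month visit falls at a different time since randomisation for each patient.

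The trial's stated purpose is to identify endpoints and supply data for sizing a larger trial. Uncertainty about when quality of life was measured weakens that product directly.

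**Working it through.** **The article's own figure.** The only power figure is a detectable standardised effect of 0.909 with 20 per arm, two-sided 5% and 80% power. A two-sample t-test calculation gives 0.9091, so it reproduces. It does not depend on the schedule, and this point does not affect it.

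**Step 1: the two schedules side by side.**

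| Assessment | Primary effect measure | Table 1 with footnote c |
|---|---|---|
| Screening | yes | yes |
| Between randomisation and treatment | yes | no |
| Day 7 (±2) | yes | no |
| Day 10 | no | yes, without origin or window |
| Discharge | yes | yes |
| 1 month (±5 days) | yes | no |
| 3 months (±14 days) | from randomisation | from consent |
| 6 months (±14 days) | from randomisation | from consent |
| 12 months (±14 days) | no | from consent |

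Counts: the definition has 7 and the table has 6. Shared: 4 (screening, discharge, 3 and 6 months). Definition only: 7 − 4 = 3. Table only: 6 − 4 = 2. Two of the four shared assessments carry different origins.

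**Step 2: can another form fill the gap?** The day-7 window is days 5 to 9. Taking 1 month as 30 days, the 1-month window is days 25 to 35. A patient discharged inside either range would have a discharge form in that window, but only by chance. No Table 1 form replaces the pre-treatment one.

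**Step 3: the effect of the clock.** Let g be the number of days from consent to randomisation. It is the sum of the consent-to-surgery interval (not stated) and the surgery-to-randomisation interval (more than 2 days, and about 28 days at the eligibility limit). Take 3 months as 90 days.

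- Definition window, in days after randomisation: 90 ± 14, i.e. 76 to 104.
- Table 1 target on the same scale: 90 − g, with window 76 − g to 104 − g.
- The target stays in the definition window if 90 − g ≥ 76, i.e. g ≤ 14.
- The two windows share at least one day if 104 − g ≥ 76, i.e. g ≤ 28. The number of shared days is 29 − g.

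Since g is not given, it is shown over an assumed range of 3 to 42 days:

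| g (days) | Table 1 target, day after randomisation | Target in 76–104? | Shared window days |
|---|---|---|---|
| 3 | 87 | yes | 26 |
| 7 | 83 | yes | 22 |
| 14 | 76 | yes | 15 |
| 21 | 69 | no | 8 |
| 28 | 62 | no | 1 |
| 35 | 55 | no | 0 |
| 42 | 48 | no | 0 |

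The same limits apply at 6 months, because the shift g and the ±14-day tolerance are unchanged.

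**Step 4: direction.** The gap g is fixed before allocation. Apart from chance imbalance, its distribution is the same in both arms, so the shift adds variability in timing and not a systematic difference between arms.

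**The case against.** The strongest case on the other side has several parts.

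- **An unseen full protocol may settle it.** The article cites a protocol version and offers the full text on demand. That would excuse an omission. It does not excuse two statements in one document that cannot both be followed.
- **Exploratory pilot.** P-values are descriptive and no superiority claim is intended. This stands, and it softens the consequence for inference. It does not help the aim of characterising endpoints.
- **Three time origins.** A reader might infer three conflicting clocks from randomisation, inclusion and consent. The article does not support that firmly. Inclusion is undefined and loosely used, since a Table 1 footnote attaches it to the screening column. But the secondary endpoints count ventilation, therapy and healing time from inclusion, which makes sense only once the leak is known. It probably lies close to randomisation, so the material conflict is between two origins.
- **Day 10 can never fall in the day-7 window.** A reader might infer this too. Footnote c gives neither origin nor tolerance. Day 10 lies outside days 5 to 9 if counted from randomisation with no tolerance. With the ±1 day that footnote b uses, it would span days 9 to 11 and touch day 9.
- **The 12-month form.** Secondary outcomes are registered for one year, so this form may simply be additional. It costs no primary assessment; its status only needs stating.

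**Conclusion.** The contradiction is real, concerns the primary endpoint and should be resolved before the first patient. Three of the seven assessments in the endpoint definition are unscheduled in Table 1, including the only post-leak, pre-treatment baseline. The 3- and 6-month visits run on a preoperative clock in one place and on randomisation in the other. Table 1's targets leave the definition's window once the consent-to-randomisation gap exceeds 14 days. How often that happens cannot be said, because the gap is not given; 28 days after surgery is the eligibility limit, not a typical interval. The day counts assume 30-day months.

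Two stronger conclusions are tempting. One is that the data would be impossible to pool. Four assessments appear in both schedules, so this goes too far. The other is that the two centres will in fact follow different schedules. The article leaves that possible but does not show it. The finding rests on the stated conflict alone.

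**What to change.** The article gives its status as not yet recruiting, so the correction can precede any data. Reconcile the Follow-up text, Table 1, footnote c and the Primary effect measure section to one quality-of-life schedule counted from randomisation. That origin is preferable because a clock started before randomisation gives each patient a different time since treatment.

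The simplest route is to bring Table 1 into line with the endpoint definition:

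- mark the questionnaire in the column before treatment and add a 1-month assessment;
- use one early in-hospital day, with a stated origin and window, in both places;
- relabel the follow-up header as time after randomisation, and use the same origin in the Follow-up text or define inclusion;
- state whether the 12-month form is an additional assessment or is removed.

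The cost is an amendment to the table, the wording and the CRF visit labels. It needs no extra patients, and no questionnaires beyond those the endpoint definition already requires.

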#### Secondary effect measures

Cure rate of patients within 44 days postoperatively. Cure is defined as follows:
○ No leak can be detected clinically, endoscopically, and/or radiologically *or*○ Patients are able to be discharged from the hospital despite persistent leakage (treated with SEMS or drainages), once they are in a clinically stable state without signs of acute inflammation and tolerate oral food intake.○ In case of death within 44 days postoperatively and persistent leak, patients are classified as “not cured.”Period of hospitalization, defined as the time in days from the day of surgery (day 0) until discharge from the hospital to ambulant or for follow-up treatment (except early rehabilitation or neurological rehabilitation)Rate of and reasons for treatment failure, defined as a necessary change of the treatment strategy or postoperative deaths, that are directly or indirectly associated with the anastomotic leakRate and type of surgical revisions with indication of the reasonsGeneral complications (surgical and non-surgical complications) and treatment-specific complications such as stent dislocations, which will be classified according to the Clavien-Dindo classification and the Comprehensive Complication Index [22]Mortality, defined as postoperative death within 30 and 90 days (30-day and 90-day mortality) and during the hospitalization period. In addition, we determined whether the patients died as a direct or indirect result of the insufficiency.Duration of intensive care treatment (starting from diagnosis of the anastomotic leak)Influence of treatment on possible sepsis, as measured by the SOFA score [26, 27]Ventilation time (measured ventilation time in hours from inclusion to extubation or continuously spontaneously breathing tracheostomized patients, respectively)Duration of therapy (from the time of inclusion until the removal of the last drainage or stent)Number of endoscopies throughout the trial with indication of number of SEMS or vacuum system replacements and/or revisionsDuration of healing (from the day of inclusion until no leakage can be detected endoscopically)Time from inclusion to oral food intakeTreatment costs (inpatient and outpatient)Occurrence of symptomatic stenosis with indication of chosen specific treatment

Secondary outcome measures will be registered up to 1 year after inclusion.

During each intervention and every study visit during the complete course of the intervention and follow-up, specific complications potentially related to the intervention are documented. AEs and SAEs are collected, and relations to the study intervention interpreted and compared between the two groups and the results published.

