### Randomization

In case of clinical, radiological, or laboratory suspicion of an anastomotic leak after Ivor Lewis esophagectomy, a diagnostic upper gastrointestinal endoscopy will be performed. If an anastomotic leak is verified endoscopically and all inclusion and exclusion criteria are met, patients will be randomly assigned to either control (SEMS) or experimental (EVT) group with a 1:1 allocation using a web-based, centralized permuted block randomization system. The allocation will be final and the researchers will not be able to influence the results. Due to the character of the intervention, a blinding is impossible.

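### Cure, hospital stay and 30/90-day mortality are counted from surgery although randomisation follows 2 to 28 days later, so patients have unequal time after randomisation and the endpoints carry avoidable noise

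*Protocol article*

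**What the plan says.** Under Secondary effect measures, three outcomes start at surgery:

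- Cure: "Cure rate of patients within 44 days postoperatively". The death rule uses the same clock: "In case of death within 44 days postoperatively and persistent leak, patients are classified as" not cured.
- Hospital stay: "defined as the time in days from the day of surgery (day 0) until discharge from the hospital".
- Mortality: "Mortality, defined as postoperative death within 30 and 90 days (30-day and 90-day mortality) and during the hospitalization period".

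Cure can be met in two ways. Either no leak is found on clinical, endoscopic and/or radiological assessment, or the patient leaves hospital stable and eating with the leak still open: "Patients are able to be discharged from the hospital despite persistent leakage (treated with SEMS or drainages").

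Randomisation comes later than surgery. The Randomization section states: "If an anastomotic leak is verified endoscopically and all inclusion and exclusion criteria are met, patients will be randomly assigned". The Exclusion criteria rule out leaks within 48 hours of surgery and leaks beyond 4 weeks. The Endoscopy section promises treatment within 12 hours of diagnosis.

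The two treatments run on different schedules. For stents: "The stent will be removed or replaced after 21 days (±2 days"). Under Intervention group (EVT), the vacuum system is exchanged or removed 3 to 5 days after placement.

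Other outcomes in the same list use a different origin. Ventilation time, duration of therapy, duration of healing and time to oral intake start at inclusion, and intensive care time starts at leak diagnosis. The article gives no reason for the surgery clock or for 44 days.

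**The concern.** Treatment can act only after randomisation. When an outcome window opens at surgery, each patient's time under comparison depends on the day the leak was found. Two patients given the same treatment can then have very different chances of being recorded as cured or dead by the cut-off, for a reason unrelated to the treatment. Hospital stay likewise includes a stretch that is fixed before allocation.

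For cure, the window also meets the stent schedule. If the leak is found late enough, planned stent removal comes after the cut-off, whereas a vacuum patient has scheduled exchanges within it.

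These are secondary and exploratory outcomes. However, the abstract names healing rate, period of hospitalization and overall mortality among the important ones, and the trial exists to find suitable endpoints and supply figures for a later sample size calculation. Event rates and SDs that mix in time before randomisation would pass into that calculation.

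**Working it through.** **The plan's own figure.** The only computed statistical figure is the detectable effect of 0.909 with 20 per arm, two-sided 5% and 80% power. The exact two-sample t calculation reproduces it (0.9091; power at 0.909 is 0.7999). This point does not depend on it.

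**Inputs.** Let L be the postoperative day on which the leak is verified and the patient randomised. The Exclusion criteria give L from just over 2 to 28. Cut-offs are days 44, 30 and 90 (Secondary effect measures). Stent dwell is 21 days, range 19 to 23 (Control group). Treatment is taken to start on day L; the 12-hour allowance changes this by at most half a day.

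**Time after randomisation.** The formulas are 44 − L, 30 − L and 90 − L. Planned stent removal is on day L + 21 (L + 19 to L + 23).

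| L | Days left to day 44 (cure) | To day 30 | To day 90 | Planned stent removal, postoperative day |
|---|---|---|---|---|
| 2 | 42 | 28 | 88 | 23 (21 to 25) |
| 14 | 30 | 16 | 76 | 35 (33 to 37) |
| 21 | 23 | 9 | 69 | 42 (40 to 44) |
| 23 | 21 | 7 | 67 | 44 (42 to 46) |
| 25 | 19 | 5 | 65 | 46 (44 to 48) |
| 28 | 16 | 2 | 62 | 49 (47 to 51) |

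The 2 days for 30-day mortality is the extreme case. More generally, for L above 15 less than half of the 30-day window lies after randomisation (30 − 15 = 15).

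**Cut-off against stent removal.** L + 21 > 44 when L > 23. With a 23-day dwell the threshold is L > 21, and with a 19-day dwell it is L > 25. The documents give no distribution for L. If it were uniform over days 2 to 28 (assumption), the share of stent patients whose planned removal falls after day 44 would be (28 − 23)/26 = 19%, with a range of (28 − 25)/26 = 12% to (28 − 21)/26 = 27%. Of 20 stent patients, 19% is about 4. This is the share not reaching planned removal, not the share unable to be classed as cured.

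**Noise in hospital stay.** Stay from surgery is L plus the stay after randomisation. If the two are independent (assumption), the variances add, and the N needed for a given difference in days grows by the factor (s² + v²)/s². Here s is the SD of the stay after randomisation and v the SD of L. Neither is given, so both are varied:

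- Uniform L: v = 26/√12 = 7.5 and v² = 56.3. With s = 10, 156.3/100 = 1.56; with s = 15, 281.3/225 = 1.25; with s = 30, 956.3/900 = 1.06.
- Clustered L, v = 3: with s = 10, 109/100 = 1.09; with s = 30, 909/900 = 1.01.

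The required N for this outcome thus rises by about 56% to 6% under uniform onset, and by 9% to 1% if leaks cluster. A positive correlation between L and later stay would raise these figures, and a negative one would lower them.

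**The case against.** The strongest reply is that L is fixed before allocation, so randomisation balances it between the arms in expectation. That is correct. For hospital stay and mortality the surgery clock introduces no systematic difference between arms; with 20 per arm, chance imbalance in L remains possible. The outcomes are secondary, p-values are described as merely descriptive, and the article disclaims any answer on superiority. It also records 90-day mortality (at least 62 days after randomisation), in-hospital mortality and overall survival, and it counts several related outcomes from inclusion. All of this limits the weight of the point.

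Two stronger readings are tempting, and the documents do not support them:

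- *A stent patient whose leak is found after day 23 cannot be counted as cured by day 44.* The cure definition accepts clinical or radiological absence of a leak, and also discharge with the leak persisting under a stent. What is lost is confirmation at scheduled removal. The discharge route names stents, and the Background section says that stents keep the passage open for oral intake while vacuum therapy rules out oral nutrition. The net effect could therefore favour either arm.
- *30-day mortality mostly counts what happened before randomisation.* Every randomised patient was alive at randomisation, so no earlier death can enter. The defect is short and unequal exposure.

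What stands is that the windows differ between patients, that time origins are mixed within one list without a reason, and that balance in expectation removes neither the noise nor the possibly different routes to cure.

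**Conclusion.** The point holds as a matter of date arithmetic. Counted from surgery, time after randomisation varies between patients from about 42 to 16 days for cure, 28 to 2 days for 30-day mortality and 88 to 62 days for 90-day mortality. Hospital stay includes up to 28 days beyond the reach of treatment.

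For stay and mortality the consequence is noise and unequal exposure, with no systematic bias shown. For cure, leaks found after about day 23 (21 to 25 across the dwell tolerance) cannot have closure confirmed at scheduled stent removal within the window. The arms may then be assessed by different routes, with a net direction that the documents do not settle.

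The date ranges need no assumption beyond treatment starting close to diagnosis. The 19% and the sample-size increases do: they rest on an unknown leak-day distribution, an unknown SD of later stay, and independence of the two. They may be close to negligible if leaks cluster in a few days, so no single figure for lost information should be quoted. This is an inexpensive improvement to endpoints meant to inform a later trial. It is not a flaw in the primary analysis.

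**What to change.** For the between-arm comparison, define these outcomes from randomisation:

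- **Cure:** status at a fixed number of days after randomisation, with the death rule on the same clock. The sponsor should set the length, give a reason, and reconcile it with the 21 ± 2-day stent schedule. Any window longer than 23 days reaches first planned removal for every patient. A second full dwell could run to 2 × 23 = 46 days.
- **Hospital stay:** days from randomisation to discharge, with the existing rule on discharge destinations.
- **Mortality:** death within 30 and within 90 days of randomisation. In-hospital mortality can stay as it is.

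Keep the from-surgery versions as descriptive results, and report the distribution of L by arm.

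The cost is small. The article gives the trial as not yet recruiting and the SAP as still to be finalised. Stay and mortality need only the dates of surgery, randomisation, discharge and death. There are two downsides. The main results become less directly comparable with surgical reports, which the descriptive versions offset. For patients already discharged, cure status at the new cut-off may have to come from records: after discharge, Table 1 schedules nothing before 3 months, and the 1-month contact listed under Primary effect measure is for quality of life.
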